### **7.5 Immunogenicity and Correlates of Protection**

#### **7.5.1 Immune Response Determined by ELISPOT Assay**

An *ex vivo* IFN- $\gamma$  ELISPOT assay will be used to assess immune response to vaccine. Descriptive statistics will be used to summarize T cell responses by treatment group and

stimulation antigen, for a subset of subjects (as in Section 3.6.4) in the PP population. Summaries will include the assessment of response at all pre- and post-vaccination immunology time points, as well as change from pre-vaccination to each post-vaccination time point.

### **7.5.2 Immune Response Determined by Intracellular Cytokine Staining Assay**

Immune response to vaccine will also be assessed by determining the percentage of CD4 and CD8 T cells that produce any of 3 cytokines (IFN- $\gamma$ , TNF- $\alpha$ , and/or IL-2) or a combination of the 3 cytokines simultaneously following stimulation with peptide pools derived from and representing the entire amino acid sequence of the mycobacterial antigen Ag85A. Response will be measured by flow cytometry in the intracellular cytokine staining (ICS) assay.

Median DMSO-subtracted cytokine responses and associated 95% confidence intervals (CI) or other descriptive statistics as appropriate will be used to summarize percentage T cell responses for a subset of subjects (as in Section 3.6.4) in the PP population. Summaries of T cell response will be presented by T cell type (CD4 and CD8) and by stimulation antigen (Ag85A). Summaries will include immune response at all available pre- and post-vaccination immunology time points, and change from pre-vaccination to post-vaccination time points.

### **7.5.3 Correlates of Protection**

Investigations for determining correlates of immune protection to tuberculosis are ongoing and the technical specifications for the assays are unknown at this time. Decisions on the technical aspects for completing the analysis of correlates of immune protection for this study will be made before the study is unblinded. Further information on the planned analysis will be provided in a separate analytic plan, when available.

### **7.5.4 Other Immunology Analyses**

Immunogenicity will be summarized by ART status at baseline, study site, and by treatment group at all time points as collected and as available, based on the PP population. Supportive analyses will also be performed based on the ITT and all randomized subjects populations, as appropriate. No imputation for missing data will be performed. Data will be transformed as appropriate prior to analysis.

### **7.5.5 Exploratory Immunology Analyses**

Analyses of other immunological assessments may be performed to further characterize the immune response to study vaccine. If warranted, results will be summarized by ART status at baseline, study site, and by treatment group at each available time point as described below for each parameter, otherwise results will be provided in subject data listings only.

### **7.5.6 Tuberculin PPD Skin Test**

Results at each available time point will be summarized using count (percentage) summaries and descriptive statistics for the tuberculin PPD skin test (measured in millimeters at the transverse induration), for all subjects in the PP population.

## **7.6 Sample Size Considerations**

The sample size for this study was selected as adequate for a review of the safety profile. Given 325 subjects receiving MVA85A/AERAS-485, the study will have a 90% probability of detecting at least one adverse event which occurs at a rate of 0.71%.

Due to the expected impact of ART on TB disease, an estimated TB disease incidence of between incidence of between 1.5% and 2.0% per year in the control group, based on the TB case definition #1, will be utilized in supportive sample size estimates for efficacy. When the true efficacy is approximately 70%, 325 subjects per treatment group (650 subjects total) will provide 81% power to demonstrate positive efficacy given a rate of 2.0% in the control group per year, or 71% power given a rate of 1.5% in the control group per year. When the true efficacy is approximately 60%, 325 subjects per treatment group will provide 67% power to demonstrate positive efficacy given a rate of 2.0% per year, or 57% power given a rate of 1.5% per year. Calculations are based on a one-sided log-rank test at a significance level of 0.10 and assume completion of enrollment in 21 months, approximately 15-month follow-up period for the last subject enrolled, and a maximum of 36 months for the first subject enrolled. A nominal estimate of approximately 2% mortality and loss to follow-up is assumed per year across ART strata.

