## 2.2 Design

This Phase II multi-country trial will be conducted as a randomized, double-blind, placebo-controlled proof-of-concept trial in 650 HIV-positive adults with no evidence of active TB disease. Subjects will be stratified at the time of randomization by whether or not they are currently receiving ART and then randomized in a ratio of 1:1 to receive either MVA85A/AERAS-485 at  $1 \times 10^8$  pfu or placebo (Candin), as shown in Table 2-1.

Randomization of each group will be capped so that at least 50% of the subjects randomized will be receiving ART at randomization. Subjects will receive an intradermal injection of MVA85A/AERAS-485 or placebo on Study Day 0, followed 6-9 months later by a booster injection of MVA85A/AERAS-485 or placebo. The minimum follow-up period for each subject will be 6 months after their last vaccination, during which subjects will be followed for safety, clinical signs and symptoms of TB, and immunogenicity. All subjects will continue to be followed every 3 months until the last subject enrolled has been followed for 6 months after their last vaccination.

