### 7.3.2 Efficacy of MVA85A/AERAS-485

For the protocol-specified secondary objective of TB disease, subjects will be evaluated for the development of TB disease throughout the study utilizing TB Case Definition Endpoint #1 as the primary disease endpoint assessment. Less stringent TB case definitions, Endpoint #2 and Endpoint #3, will also be evaluated with no adjustment for multiplicity performed; it is acknowledged that the overall Type I error probability is not controlled in the evaluation of these endpoints.

The incidence of TB disease will be calculated as the number of new cases of TB disease in the PP population with a date of diagnosis from 28 days post-Study Day 0 vaccination through the end of study follow-up (as defined for each subject), divided by the total person-time of observation. Person-time observation will be calculated based on subject date of last contact with the study minus the date of Study Day 0 vaccination; sensitivity analyses will be performed to examine time at risk of TB based on INH treatment.

The primary statistical method to be used in the analysis of TB Case Definition Endpoints #1-3 will be vaccine efficacy (VE), estimated as 1-estimated hazard ratio, based on a Cox regression analysis of time to event for each Endpoint utilizing a model containing treatment group, ART status, and study site, performed on the PP population.

Time (months) to initial TB diagnosis for each Endpoint #1, #2 and #3 from Study Day 0 vaccination in each treatment group will be examined using the Kaplan-Meier estimate of the survival function, based on the PP population. Kaplan-Meier curves will be displayed by ART status and treatment group, over time (months) in study (time from Study Day 0 vaccination) to event. Summaries of median time (in months) to initial TB diagnosis and associated two-sided 95% confidence intervals will also be presented for each case definition endpoint. Time to initial diagnosis for each case definition endpoint will be compared using a two-sided log-rank test, stratified by study site and ART status at baseline. As a supportive analysis, the exact binomial (Clopper-Pearson) method will also be used to estimate VE and its corresponding two-sided 95% confidence interval conditional on the total number of events, and corresponding p-value, for each case definition Endpoint. All summaries will be presented by ART status and treatment group for subjects in the PP population.

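### The efficacy power in Section 7.6 is for a one-sided 0.10 log-rank test, but Section 7.3.2 plans a two-sided test with no stated alpha; the two sections need one criterion

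*Protocol*

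**What the plan says.** Section 7.6 first justifies 325 subjects per group by the safety review, and then offers efficacy power as supportive. For VE 70% it states "81% power to demonstrate positive efficacy given a rate of 2.0% in the control group per year, or 71% power" at 1.5% per year. For VE 60%, "325 subjects per treatment group will provide 67% power to demonstrate positive efficacy given a rate of 2.0% per year, or 57% power" at 1.5% per year. The basis follows: "Calculations are based on a one-sided log-rank test at a significance level of 0.10", with enrolment over 21 months, about 15 months of follow-up for the last subject, at most 36 months for the first, and about 2% per year mortality and loss.

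Section 7.3.2 sets out the analysis of the same TB endpoints. The primary method is "vaccine efficacy (VE), estimated as 1-estimated hazard ratio, based on a Cox regression analysis of time to event", with no alpha or interval level given. Time to diagnosis "will be compared using a two-sided log-rank test, stratified by study site and ART status at baseline", again with no alpha. A supportive exact binomial method will "estimate VE and its corresponding two-sided 95% confidence interval conditional on the total number of events". The only other interval level there, also 95%, is for median time to diagnosis.

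Section 2.2 says: "The minimum follow-up period for each subject will be 6 months after their last vaccination", with the boost given 6-9 months after the first injection.

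**The concern.** Power describes one decision rule. Section 7.6 uses a one-sided 10% rule. Section 7.3.2 specifies a two-sided test, and the one level it attaches to a VE interval is 95%. Both are current text, and a separate analysis plan could add an alpha but could not make the two statements agree as they stand.

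What is at stake is how a null efficacy result is read. With about 13 to 19 expected cases in total, a non-significant result may well be set against the 81% or 71% in Section 7.6. If it was judged at a stricter two-sided threshold, the chance of success was lower than those figures say.

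**Working it through.** **Inputs (Section 7.6).** 325 per arm; control rate 2.0% or 1.5% per year; VE 70% or 60% (hazard ratio HR 0.30 or 0.40); 21 months of accrual; follow-up 15 to 36 months; 2% per year loss.

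**My assumptions.** Uniform accrual; exponential event and loss times; annual figures read as annual risks, so the hazard is -ln(1 - 0.02) = 0.0202 for both the higher control rate and the loss. Reading them directly as hazards changes the formula results below by less than one point.

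**Expected events.** For a subject followed t years, with event hazard λ and loss hazard δ, the event probability is λ/(λ+δ) × (1 - exp(-(λ+δ)t)). It is averaged over t uniform on 1.25 to 3 years and multiplied by 325 per arm. Total events D, in Section 7.6 order, are 17.40, 13.08, 18.75 and 14.09.

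**Power formulas.** Power = Φ(θ - z), where z = 1.282 (one-sided 0.10), 1.645 (two-sided 0.10) or 1.960 (two-sided 0.05).
- Freedman: θ = √D × (1 - HR)/(1 + HR)
- Schoenfeld: θ = √D × |ln HR|/2

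Worked case, VE 70% at 2.0%, Freedman: θ = 4.171 × 0.7/1.3 = 2.246. One-sided 0.10: Φ(0.964) = 83%. Two-sided 0.05: Φ(0.286) = 61%.

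**Re-anchoring the protocol's own figures.** θ = Φ⁻¹(stated power) + 1.282. For 81%: 0.878 + 1.282 = 2.159 (unrounded inputs). Two-sided 0.05 power is then Φ(2.159 - 1.960) = 58%.

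**Simulation.** 20,000 trials per scenario, unstratified log-rank, annual rates taken as hazards.

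| Method | One-sided 0.10 | Two-sided 0.10 | Two-sided 0.05 |
|---|---|---|---|
| Stated in 7.6, re-anchored to the right | 81/71/67/57 | 70/58/53/43 | 58/45/41/31 |
| Freedman | 83/75/72/63 | 73/62/58/49 | 61/50/46/36 |
| Schoenfeld | 89/81/76/67 | 81/70/63/53 | 71/59/51/41 |
| Simulation | 86/77/73/65 | 75/64/60/50 | 63/50/47/36 |

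All entries are percentages in Section 7.6 order (VE 70% at 2.0%, 70% at 1.5%, 60% at 2.0%, 60% at 1.5%).

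**Reproduction.** None of these log-rank methods, run on the stated inputs, returns all four stated figures. They come out above the stated values at one-sided 0.10, so the stated figures err on the cautious side.

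**Size of the change.** Read within a row, so that only the criterion moves, going from one-sided 0.10 to two-sided 0.05 costs about 18 to 29 percentage points. Going to two-sided 0.10 costs about 8 to 15.

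**Follow-up.** A boost at 6 to 9 months plus 6 months gives 12 to 15 months for the last subject, so Section 7.6 uses the top of that range. With 12 to 33 months, Freedman at one-sided 0.10 gives about 80/71/68/59%, within about 2 points of all four stated figures. Simulation at two-sided 0.05 gives about 58/44/42/32%.

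**The case against.** The strongest reply is that two-sided 0.05 is an inference. Section 7.3.2 gives no alpha for the log-rank test or the Cox estimate, and the 95% VE interval belongs to a supportive exact method. An alpha may be set in the analysis plan, which is not at hand. This stands, so the two-sided 0.05 figures are conditional. It does not rescue the stated power: a two-sided log-rank test has the power of the Section 7.6 test only at two-sided 0.20, a level no section names. For the exact method that does carry the 95% interval, power is lower still, about 53/39/37/27% (Poisson total of cases, binomial split between arms).

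A reader might go further in three ways that the documents do not support.
- **That the trial really has some single lower power, such as 63%.** The result depends on the formula and on an unstated alpha, and setting 81% beside a simulated 63% mixes two models. Nor can one say that a 70% effective vaccine would be missed more than a third of the time: Schoenfeld gives 71% at 2.0% per year, a miss rate of 29%.
- **That the stated figures contain an arithmetic error.** The mismatch depends on the formula and runs in the cautious direction.
- **That the 15-month assumption inflates the stated power.** It is a declared planning value inside the range the design allows, and the stated figures are close to what 12 months gives under Freedman.

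It is also fair to say that efficacy is a secondary objective, that Section 7.6 calls these estimates supportive, and that sidedness and alpha are printed beside them. That limits the importance of the point.

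**Conclusion.** The inconsistency is real: Section 7.6 reports power for a one-sided 0.10 log-rank test, and Section 7.3.2 plans a two-sided one with no alpha and never uses the one-sided 0.10 criterion.

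If two-sided 0.05 is intended, log-rank power in Section 7.6 order is roughly 58-71 / 45-59 / 41-51 / 31-41%. If two-sided 0.10 is intended, it is about 73-81 / 62-70 / 58-63 / 49-53% from Freedman to Schoenfeld, with the re-anchored figures lower. At two-sided 0.10, Schoenfeld comes close to the stated 81% and 71%, but only because that formula starts from 89% and 81% at one-sided 0.10.

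These ranges rest on uniform accrual, exponential times and the other Section 7.6 inputs. The point should be fixed, but the sample size and the primary safety analysis do not depend on it.

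**What to change.** Name one test, its sidedness and its alpha in both sections. Either:

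1. State in Section 7.3.2 that the proof-of-concept criterion is the stratified log-rank test at one-sided 0.10 (in effect, a two-sided 80% interval for VE lying above 0), and keep the 95% interval for estimation. The Section 7.6 figures then describe the planned test.
2. Keep the two-sided test, give its alpha, and restate the Section 7.6 power for it, in that section's scenario order and with the calculation method named.

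Under either option, say how the criterion relates to the primary Cox estimate of VE. Optionally, quote power for 12 as well as 15 months of last-subject follow-up.

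The cost is wording only, with no extra subjects. The second option makes the stated power less favourable.

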## **7.7 Interim Immunogenicity Review**

The sponsor may conduct a review of immune response data prior to database lock after immunogenicity results are available for the first 70 subjects. Aggregate data will be presented at selected time points and will be presented identified only by a blinded label (e.g., ‘Group A’ and ‘Group B’). Review of these data will allow the sponsor to determine if there is evidence of any immune response prior to completion of the trial. No decision cut points or stopping rules will be stipulated, no changes to monitoring practices or study procedures will be implemented following the reviews, and the study will continue following the reviews. No hypothesis testing will be performed.

Data summaries for preliminary immunogenicity review using blinded labels will be prepared by a statistician who is not the study statistician and who is not involved in study design, conduct, or analyses. Immunology technicians will perform all assays in a blinded manner. Data identified for inclusion in the immunogenicity summaries will be cleaned prior to analysis.

## **7.8 Safety Reviews**

The DMC will convene to review safety data (including CD4 counts) as described in Section 5. The DMC will conduct a second unblinded-by-group safety and risk review after the 600th subject enrolled completes one month of follow-up post-vaccination. The DMC will evaluate blinded and unblinded-by-group safety data to determine if a pattern of adverse events related to MVA85A/AERAS-485 or other safety or risk concerns exist. Both blinded and unblinded analyses will be described in a statistical analysis plan, and unblinded reviews will be prepared for the DMC by an unblinded statistician not associated with the study conduct or primary

analyses. All procedures associated with this review, including objectives, data handling, and elements to be included for review will be documented in the DMC minutes.

## **7.9 Final Study Report**

A final study report will be prepared after database lock is completed for all data collected through the final assessment of the study.

Modifications or additions to the analyses described above will be included in the relevant statistical analysis plan(s). Any decisions to deviate from the planned analyses described in the protocol and in the statistical analysis plan will be described in detail in the final study report.

## **7.10 Computer Methods**

Statistical analyses will be performed using SAS® version 9.1 or later under a Windows operating system.

# **8 DATA COLLECTION, MONITORING, AND RECORD RETENTION**

For the purpose of monitoring and auditing the study, source documentation will consist of existing medical records and/or study records developed and maintained by the investigator. Any source document templates provided by Aeras or its designee will serve as supplements to the subject's study record.

Data recorded on source documents will be entered using electronic case report forms (eCRFs) using an Electronic Data Capture (EDC) system provided and approved by Aeras.

The study will be monitored regularly by Aeras or its designee throughout the study period. For studies of unapproved investigational products, all study records (source documents, signed informed consent forms, IRB/IEC correspondence and approval letters, study vaccine management records) will be kept secured for a minimum of two years following the marketing of the investigational product or for 2 years after the discontinuation of the IND (or CTA, etc.). The investigator will ensure that study records are not disposed of or removed from the clinical site without prior notification and approval from Aeras or its designee.

# **9 HUMAN SUBJECTS**

## **9.1 Ethics and Regulatory Considerations**

The study will be conducted in compliance with country specific laws and regulatory requirements. The conduct of the study will also adhere to the GCP principles laid out by the International Conference on Harmonization and the Declaration of Helsinki.

The protocol and informed consent form will be reviewed and approved by the IRB or IEC of each participating clinical site prior to any protocol-specified procedures being conducted. The

investigator will inform the IRB/IEC as to the progress of the study on a regular basis, or at minimum, once a year. Aeras will also have an independent IRB review and approval of the protocol and informed consent form and will keep the IRB informed of the progress of the study.

Written informed consent will be obtained from each subject prior to any protocol-specified procedures being conducted.

To maintain confidentiality, subject identification numbers will be used to identify the subject's laboratory specimens, source documents, CRF, study reports, etc. All study records will be maintained in a secured location. Clinical information will not be released without written permission from the subject except as necessary for monitoring or auditing of the study by Aeras or its designee or applicable regulatory authorities.

## **9.2 Institutional Review Board or Independent Ethics Committee**

All the documents the IRB/IEC may need to fulfill its responsibilities, such as the protocol, protocol amendments, information concerning subject recruitment, payment or compensation procedures, etc., will be submitted to the IRB/IEC by the investigator. The IRB's/IEC's written, unconditional approval of the study protocol and the informed consent form will be in the possession of the investigator/clinical site staff prior to the conduct of any protocol-specified procedures.

Modifications to the protocol may not be implemented without prior written IRB/IEC approval except when necessary to eliminate immediate hazards to the subjects or when the modification involves only logistical or administrative aspects of the study. Such logistical or administrative modifications will be submitted to the IRB/IEC in writing by the investigator, and a copy of the correspondence to verify the submission will be maintained.

The investigator must inform the IRB/IEC of modifications to the informed consent form or any other documents previously submitted for review/approval, of any new information that may adversely affect the safety of the subjects or the conduct of the study, provide an annual update and/or request for re-approval, and advise the IRB/IEC when the study has been completed.

Any documents or forms to be provided to the subject (e.g., information cards, form letters from the investigator), and all forms of study advertising (flyers, brochures, print advertisements, radio or television scripts, etc.) must be approved by Aeras or its designee prior to the clinical site submitting them to the IRB/IEC. Approval from the IRB/IEC must be obtained prior to providing the documents or forms to the subject.

## **9.3 Informed Consent**

The principles of informed consent in the current edition of the Declaration of Helsinki and ICH-GCP should be implemented prior to any protocol-specified procedures being conducted. Informed consent will be documented in writing on a consent form approved by the IRB/IEC.

All relevant information should be provided in both oral and written form in a way that is understandable to the subject. Ample time and opportunity must be given for the subject to inquire about details of the study. The written consent document will embody the elements of informed consent as described in the Declaration of Helsinki and will also comply with local regulations.

The investigator or the investigator's qualified designee will explain the nature of the study and inform the subject that participation is voluntary and that the subject can withdraw at any time. The subject must be informed about the study's purpose including why the subject was selected to participate, study goals, expected benefits and risks, potential risks, and that some potential risks are unforeseeable. The individual must be provided with a description of the procedures and the estimated duration of time required for participation in the study, as well as alternative interventions or courses of treatment, if applicable.

The subject must receive an explanation as to whether any compensation and any medical treatments are available if injury occurs and, if so, what they are, where further information may be obtained, and who to contact in the event of a study-related injury. Individuals must be told who to contact for answers to any questions related to the study.

The subject must be informed that their participation is voluntary and that they are free to withdraw from the study for any reason at any time without penalty or loss of benefits to which they are otherwise entitled. The extent of the confidentiality of subject records must be defined and the subject must be informed that applicable data protection legislation applies.

The subject must be informed that the monitor(s), auditor(s), IRB/IEC members, and the applicable regulatory authorities will be granted direct access to the subject's original study medical records for verification of protocol-specified procedures and/or data, without violating the confidentiality of the subject to the extent permitted by the applicable laws and regulations. The subject must be informed that his/her signature on the informed consent form indicates that he/she has decided to participate in the study, having read and discussed the information presented.

Modifications made by the investigator to an informed consent form template provided to the investigator by Aeras or its designee will be reviewed and approved by Aeras or its designee prior to being submitted to the IRB/IEC.

The original, signed informed consent form for each subject will be maintained by the investigator as part of the subject's study records. A copy of the signed informed consent form will be provided to each subject.

